### Blinding

Randomization and group allocation will be performed by a staff assistant not involved in any other aspect of the research. Outcome measures will be collected by a research assistant blind to group allocation, with a formal request not to discuss any aspect of the study with the participants. Data analysis will be conducted by a staff member blind to the nature of the interventions and not engaged in any other aspect of the study. Due to the characteristics of the study, the research assistant conducting the treatments cannot be blinded, nonetheless, this research assistant will not be involved in any of the above procedures. Blinding of participants will be analysed using a three point scale, following specific orientations for this purpose [51].

### Statistical analysis

Data will be analysed using the Statistical Package for Social Science software (SPSS v.20, Inc., Chicago, USA). The analyses will be conducted considering a statistically significant *p*-value ≤0.05. Data normality of the study will be assessed with the Kolmogorov-Smirnov test and homogeneity with the Levene’s test. The results will be reported as the mean with corresponding 95% confidence interval. Intention-to-treat analysis will be conducted so that all patients are analysed within their group allocation. Drop-outs and their reasons will be informed. All data input will be kept in two different files (double data entry) that will be updated every week by a research assistant.

A two-way analysis of variance will be conducted to assess between and within groups differences. For the primary outcome measures (SPADI and NPRS) a 2 × 3 ANOVA with treatment group (EG versus CG) and time (baseline, end of the treatment and follow-up) factors will be performed. Separate 2 × 2 ANOVA will be used for ROM (baseline and end of the treatment period), and a 2 × 3 ANOVA will be conducted for self-efficacy (baseline, end of the treatment period and follow-up). Additionally, appropriate post-hoc tests (Bonferroni) will be used if prior analysis indicates significant differences. GROC analysis will be conducted using descriptive statistics and participants will be classified according to treatment success. Those reporting + 5 or more will be classified as successful. Within groups differences will be calculated at the end of the treatment period and follow-up, and effect sizes will be calculated using Cohen effect size (0.2–0.5: small effect, 0.5–0.8: moderate effect, 0.8 or more: large effect size).

A second study will explore changes in expectation throughout treatment descriptively and whether those differences are associated with SPADI, NPRS and group allocated. Therefore, an ANCOVA will be conducted to analyze the influences of covariates (expectation and self-efficacy) on SPADI and NPRS. A separate 2 × 3 ANOVA will be used to examine PPT measurements in the three different body areas. Post-hoc tests (Bonferroni) will be used if prior analysis indicates significant differences.

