### Participant timeline

The enrollment process will begin from the end of February 2020. After entering the study, participants will have the following outcomes assessed at baseline: SPADI, NPRS, AROM, PPT, expectations and SE; at the end of the treatment period: SPADI, NPRS, AROM, PPT and GROC; and at one month follow-up: SPADI, NPRS, and GROC. Expectation is the only outcome measure to be collected during the third week of treatment. Figure 2 depicts enrolment, interventions and assesssments timeframes throughout the study. Participants will attend ten individual sessions, twice a week (approximately 40 min each), in either of the available treatment sites, according to their geographic locations (see study settings). For the follow-up, participants will be contacted by a research member via email or mail to fill out the respective outcome measures. A telephone call will be made for participants that miss one treatment session without providing explanations.

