### Sample size

In order to calculate the number of subjects to be included in this study an alpha value of 0.05 and power of 80% was chosen together with a minimal clinically important difference of 10 points on the SPADI scale with standard deviation of 13.5 points [26]. An initial number of 28 participants in each group was required based on this calculation. With an estimated 20% loss to follow-up, we planned to recruit a total of 70 subjects (35 in each group).

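### The primary 2 × 3 ANOVA is paired with an intention-to-treat promise but with no missing-visit method; unless values are imputed first, up to about 14 of 70 randomised participants drop out of it

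*Protocol article*

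**What the plan says.** All references are to the Methods of the protocol article.

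- **Population.** Statistical analysis: "Intention-to-treat analysis will be conducted so that all patients are analysed within their group allocation". The abstract repeats that intention to treat will be adopted.
- **Method.** The same section specifies, for the two primary outcomes, "a 2 × 3 ANOVA with treatment group (EG versus CG) and time (baseline, end of the treatment and follow-up) factors will be performed". A design of the same shape is set for self-efficacy.
- **Drop-outs.** The only provision is "Drop-outs and their reasons will be informed". No imputation, carry-forward or mixed model is named anywhere in the article.
- **Expected loss.** Sample size: 28 per group are required, and then "With an estimated 20% loss to follow-up, we planned to recruit a total of 70 subjects (35 in each group").
- **Collection of the last visit.** Participant timeline: "For the follow-up, participants will be contacted by a research member via email or mail". Treatment itself is given in ten attended sessions.

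**The concern.** Time is a within-participant factor here, because the same people are scored at baseline, discharge and one month. The conventional repeated-measures ANOVA needs a complete set of scores from each person and removes anyone with a gap. The article promises to analyse all patients, expects a fifth of them to be lost, and names a method that by default leaves those people out.

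The least obvious consequence is at discharge. Someone who attends treatment and gives a discharge SPADI, but does not return the mailed or emailed form a month later, is also removed from the end-of-treatment comparison, although that score is in hand.

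Two things are at stake. Randomisation protects the comparison of everyone randomised, not of those who happen to complete every visit. And a result labelled intention to treat would rest on a selected subset.

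**Working it through.** **1. The plan's own figures.** Inputs from Sample size: difference 10 points, SD 13.5, "an alpha value of 0.05 and power of 80% was chosen", 20% loss. Sidedness is not stated; two-sided is assumed.

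- n per arm = 2 × [13.5 × (1.960 + 0.842) / 10]² = 28.6. The article gives 28, which is close enough to count as reproduced.
- Inflation: 28 / (1 − 0.20) = 35 per arm, 70 in total, exactly as stated.

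The sample size is not the problem.

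**2. Who is left in a complete-case 2 × 3 ANOVA.**

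| Loss at any visit | Excluded of 70 | Analysed |
|---|---|---|
| 10% | 7 | 63 |
| 20% (planned) | 14 | 56 |
| 30% | 21 | 49 |

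Only the 20% row is the plan's; the others show the range.

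**3. Power.** The standardised difference is 10/13.5 = 0.741. Normal approximation: power = Φ(10 / (13.5 × √(2/n)) − 1.96).

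- n = 28: Φ(2.772 − 1.96) = 0.791; by the t-test, 0.777.
- n = 35: Φ(3.099 − 1.96) = 0.873; by the t-test, 0.863.

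The second line applies at discharge only if nobody is lost during the five treatment weeks. Let k of the 14 be lost before discharge. A method that uses observed scores then has 70 − k discharge scores, against 56 for the complete-case ANOVA. With k = 0 that is 35 per arm (86%); with k = 14 it is 28 per arm (78%) and nothing is gained. The article does not say when the loss is expected, so the gain lies somewhere between.

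**4. Can bias arise?** This is a simulation under assumed inputs, not a forecast. Assumptions: 35 per arm, true difference 10, SD 13.5, correlation between visits 0.5 to 0.7, and about 20% loss at follow-up (on average 53 to 56 of 70 complete).

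- Loss unrelated to outcome: the completers' follow-up difference averages 10.0 to 10.1, so there is no bias.
- Loss depending on the discharge score in opposite directions in the two arms (log-odds slope 0.5 to 1.0 per SD): the completers' follow-up difference averages 11.4 to 13.9. An estimator that uses the observed earlier visits gives 10.0 to 10.1.
- At discharge, a run under the same kind of mechanism gave 13.6 among completers and 10.0 when all observed discharge scores were used.

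Reversing the direction of loss in the two arms would reverse the bias. The simulation shows that bias can occur and that keeping the observed scores removes it when loss depends only on those scores. It does not show that bias will occur in this trial.

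**The case against.** The strongest reply is that the conflict depends on silence. An ANOVA excludes people only if gaps are left unfilled. The article neither says complete cases will be used nor rules out imputation, and an analysis plan that is not shown could impute first and satisfy both sentences. This stands. A reader might infer that the stated method cannot deliver intention to treat, or that the primary result is certain to be a completers' analysis. The article does not support either.

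Other points on that side:

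- **The term repeated measures is not used.** True: the text says two-way and 2 × 3 ANOVA and names no SPSS procedure. But the other reading, an ordinary two-way ANOVA on all rows, would treat three scores from one person as independent, so it is no defence.
- **The intention-to-treat sentence may mean only that nobody switches group.** That reading is possible. The literal wording also covers all patients, and a reader of the results would take it so.
- **Inflating 28 to 35 does not reveal a completers' plan.** Agreed. It is routine under any analysis, and it keeps power near the planned 80%. It supplies only the size of the expected loss.
- **A mixed model does not rescue everyone.** Agreed. With baseline as a covariate, a participant with no post-baseline score adds nothing to the treatment contrast. With baseline as an outcome visit that participant stays in the model but still says little about the effect. If loss depends on unseen scores, a missing-at-random model can be biased too.

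A reader might also infer that loss here is likely to follow response, or attach a number of SPADI points to the bias. The article gives no loss by arm and no outcome of lost participants, so neither can be supported.

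The objection does not remove the point. The article itself fixes the population, the method and an expected 20% loss, and these agree only through a step it does not name.

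**Conclusion.** The point holds in a limited form. As written, and unless values are imputed first, the primary analysis of SPADI and NPRS would leave out up to about 14 of 70 randomised participants, some perhaps with usable discharge scores, and would not match its intention-to-treat label. The self-efficacy 2 × 3 ANOVA has the same weakness.

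This rests on three assumptions: time is handled as a within-participant factor, no imputation is specified elsewhere, and realised loss is near the planned 20%. The main harm is possible bias of unknown size and direction rather than lost power. It should be fixed; it does not invalidate the design.

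**What to change.** Make the primary analysis of SPADI and NPRS a likelihood-based mixed model for repeated measures with group, visit and group-by-visit. It should use every observed score of every randomised participant in the assigned group, whatever their attendance. Enter baseline either as an outcome visit with a common mean across arms, which keeps participants with only baseline data in the model, or as a covariate. Multiple imputation before the ANOVA is an acceptable alternative.

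Then:

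- state that the analysis assumes data are missing at random;
- add a sensitivity analysis for participants with no post-baseline score;
- keep the complete-case ANOVA, if wanted, only as a sensitivity analysis;
- apply the same to the self-efficacy 2 × 3 ANOVA.

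The cost is wording, slightly more analysis work and reliance on the missing-at-random assumption. No new data are needed. The choice should be fixed before unblinded data are analysed, so that the results cannot influence it.

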### Allocation

Participants will be stratified by pain followed by sequence generation, using a computer generated random numbers. In order to reduce predictability of random sequence, blocks of 4 and 6 random numbers will be used. Allocation sequence will be placed in sequentially numbered opaque, sealed envelopes. All allocation procedures will be conducted by a research assistant not involved in any other aspect of the study.

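### The primary 2 × 3 ANOVA uses baseline as an outcome level, adjusts for neither baseline nor pain stratum, and names no deciding term; a baseline-adjusted model would be clearer and usually more powerful at almost no cost

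*Protocol article*

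**What the plan says.** The Statistical analysis section of the protocol article introduces the method in general terms: "A two-way analysis of variance will be conducted to assess between and within groups differences". For the two primary outcomes it fixes the model: "For the primary outcome measures (SPADI and NPRS) a 2 × 3 ANOVA with treatment group (EG versus CG) and time". It then lists the time levels: "time (baseline, end of the treatment and follow-up) factors will be performed". Bonferroni post-hoc tests follow only if the ANOVA is significant. AROM gets a 2 × 2 ANOVA in which baseline is again one of the time levels.

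The Allocation section says: "Participants will be stratified by pain followed by sequence generation, using a computer generated random numbers". No pain-stratum term appears in the analysis model. The only ANCOVA in the document belongs to a second study and adjusts for expectation and self-efficacy, not for the baseline score.

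The Sample size section plans for a simple comparison of two means: "an alpha value of 0.05 and power of 80% was chosen", with a "minimal clinically important difference of 10 points on the SPADI scale with standard deviation of 13.5 points".

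**The concern.** Baseline is measured before treatment, so randomisation makes its expected group difference zero. Once baseline is an outcome level, the ANOVA offers two candidate treatment tests that answer different questions. The group main effect averages the pre-treatment zero with the post-treatment effects. The group-by-time interaction is a 2-df test that the profiles differ; it does not itself say by how much at discharge or at one month. The text does not say which of the two decides.

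The only stated route to a visit-specific comparison is a post-hoc test behind the omnibus result, with no correction for chance baseline imbalance. Baseline scores and the pain stratum are both available, but neither is used as a covariate. At stake are the power of a 70-patient trial, the clarity of its main result and, if either omnibus term could be claimed, the type I error.

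**Working it through.** **Inputs from the Sample size section:** difference 10 points, SD 13.5, alpha 0.05 (taken as two-sided), power 80%, 28 per group before loss, 35 after 20% loss.

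**Assumed, because the document does not give them:** 13.5 is the SD of a score at each visit; the within-patient correlation ρ is 0.3–0.7; for the formulas, ρ is equal between all pairs of visits; the effect is 10 points at both post-treatment visits.

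**1. The plan's own figure.** n = 2 × [13.5 × (1.960 + 0.842)/10]² = 28.6 per group, which rounds up to 29 against 28 stated. This is close enough to confirm an unadjusted comparison of two means. 28/0.8 = 35 per group, 70 in all. The t-test power at 28 per group is 78%. This calculation matches neither ANOVA term.

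**2. Group main effect.** Expected difference = (0 + 10 + 10)/3 = 6.67 points. If the effect falls to 5 at follow-up, it is (0 + 10 + 5)/3 = 5.0; if it is gone by then, 10/3 = 3.33. The SD of a patient's three-visit mean is 13.5 × √[(1 + 2ρ)/3], and the standard error is that SD × √(2/28). For ρ = 0.5 this gives 11.02 × 0.267 = 2.95, so the noncentrality is 6.67/2.95 = 2.26.

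**3. Interaction.** The visit differences deviate from their mean by −6.67, 3.33 and 3.33, with sum of squares 66.7. The noncentrality is (28/2) × 66.7 / [13.5² × (1 − ρ)] = 5.12/(1 − ρ), on 2 and 108 df. The contrast of baseline with post-treatment keeps the full 10 points.

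**4. Baseline-adjusted ANCOVA at one visit.** The residual SD is 13.5 × √(1 − ρ²). For ρ = 0.5 it is 11.69, the standard error is 3.12 and the noncentrality is 3.20.

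| Power at 28 per arm | ρ = 0.3 | ρ = 0.5 | ρ = 0.7 |
|---|---|---|---|
| Group main effect | 70% | 60% | 53% |
| Group-by-time interaction | 66% | 81% | 96% |
| Unadjusted score, one visit | 78% | 78% | 78% |
| ANCOVA, one visit | 81% | 88% | 97% |

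Simulation, including unequal correlations, agrees and gives overall ranges of about 52–70% (main effect), 66–97% (interaction) and 80–97% (ANCOVA). ANCOVA exceeds the interaction by 11–15 points at ρ = 0.3, about 7 at 0.5 and about 1 at 0.7.

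**5. The gate.** Suppose success needs a significant interaction and also a Bonferroni-significant group difference at end of treatment, with three comparisons assumed because the family is not stated. Simulated power is then about 49–60% (46% if all three correlations are 0.3). Part of this loss comes from testing at one third of alpha, so it is not a like-for-like comparison with ANCOVA of one named contrast at 5%.

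**6. Type I error.** If either omnibus term alone may be claimed, and the two are treated as independent, the rate is 1 − 0.95² = 9.75% per outcome (simulated 9.5–10.5%). If a Bonferroni-significant post-treatment difference between groups is also required, the simulated rate is 3.3–3.6% with two comparisons and 2.4–2.5% with three.

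**The case against.** The strongest reply is that in a group-by-time design the interaction is the usual treatment test, and it is not diluted. At ρ of 0.5 or more it reaches the planned 80%. The raw difference between groups at each post-treatment visit is unbiased under randomisation, so chance baseline imbalance costs precision, not validity. All of this stands.

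A reader might therefore infer too much in four ways:

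- **That the trial's treatment effect is diluted by a third.** This holds only for the group main effect, and is exactly a third only with equal effects at both post-treatment visits. The protocol does not make that term decisive.
- **That the model cannot estimate the treatment effect.** Its visit-specific means do so without bias.
- **That the type I error is doubled.** This requires accepting either omnibus term alone. The text adds a Bonferroni step, and requiring a significant group difference there brings the rate below 5%.
- **That omitting the pain stratum invalidates the test.** The omission leaves the estimate unbiased and usually makes standard errors conservative. The pain measure and cut-point are not given, so the gain from including it cannot be computed.

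It can also be said that an article leaves the exact contrast to an analysis plan. That is fair for the unnamed term taken alone. It does not cover what the article does fix: baseline as an outcome level, a model of group and time only, and post-hoc tests conditional on the omnibus result.

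**Conclusion.** The point holds as a should-fix improvement to a stated method; the planned analysis is not invalid. Read as the main effect, the analysis targets 6.7 points instead of 10 and has about 52–70% power. Read as the interaction, it loses only efficiency: 11–15 points of power against ANCOVA at a correlation of 0.3 and next to nothing at 0.7. A strict chain of interaction plus a Bonferroni test at end of treatment falls to about 49–60%. A type I error near 10% per outcome arises only if either omnibus term may be claimed alone.

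These sizes rest on 28 per arm, 13.5 as the SD of a score, a 10-point effect at both post-treatment visits and correlations the document does not state. The dilution of the main effect does not depend on the correlation; the power figures do.

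**What to change.** For SPADI and NPRS, analyse the end-of-treatment and follow-up scores in one ANCOVA or mixed model with group, time, group × time, the baseline value of the outcome and the pain stratum used at randomisation. Report the adjusted group difference with its 95% CI at each visit, not conditional on an omnibus test. State before unblinding which visit contrast decides; that choice is the sponsor's. For AROM, use ANCOVA of the end-of-treatment value adjusted for baseline and pain stratum.

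The pain stratum is included because the randomisation uses it; no specific gain is claimed for it. The cost is a change of wording and a few degrees of freedom. No extra patients or measurements are needed: baseline SPADI, NPRS and AROM are already in the Participant timeline, and the stratum is known at randomisation.

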### Harms

Due to the nature of this study, we understand that it is important to control for adverse events that might occur as a result of the procedures applied. In order to monitor these, this study will use an adapted questionnaire [52], were participants will respond to the following question: “Have you experienced any discomfort or unpleasent sensation as a result of this treatment?”. Participants will inform (discomfort, soreness, fatigue, etc), rate their sensation using the NPRS (0–10, 10 meaning highest value) and inform when it started (< 30 min after treatment, between 30 min - 4 h, etc) and if it has affected their home or work activities (nothing, little or much). This scale will be applied at each treatment session.

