### Eligibility criteria

Inclusion and exclusion criteria can be found in Table 1. Criteria utilized are similar to studies investigating the use of manual therapy treatment procedures with or without exercise in patients with rotator cuff related pain [18, 19, 25–28].

**Table 1 Tab1:** Inclusion and exclusion criteria

Inclusion criteria	Exclusion criteria
1. Age 18–65 years.	1. Shoulder pain following a traumatic event.
2. Unilateral shoulder pain of atraumatic origin.	2. History and clinical presentation compatible with complete rotator cuff and/or biceps brachii rupture.
3. Scoring at least 3 out of 10 on a numeric pain rating scale.	3. Adhesive capsulitis.
4. Symptoms lasting more than 6 weeks.	4. History of dislocation.
5. Pain on active shoulder movement.	5. Glenohumeral osteoarthritis.
6. Pain provoked by at least three of the following tests: Hawkins-Kennedy, Neer, Painful arc, Empty/full can and Resisted external rotation.	6. Cancer
7. Patients referred by a shoulder specialist with diagnosis of rotator cuff injury (tendinitis/tendinosis), subacromial impingement syndrome, bursitis, subacromial pain, that fulfill the criteria above.	7. Systemic, local or auto-immune inflammatory conditions.
	8. Previous shoulder or neck surgery or fracture.
	9. Familiar pain provoked by neck movements.
	10. Presence of radicular signs.
	11. Use of corticosteroids over the past six months.
	12. Diagnosis of fibromyalgia.
	13. Clinical depression.
	14. Participants under treament for his/her shoulder condition over the last 3 months.

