### Control group (CG)

#### Exercise programme

Exactly the same as the experimental group and conducted in the same way.

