#### Sham mobilisation with movement (MWM)

The participant and physiotherapist will decide on one active shoulder movement that is more functionally relevant to the individual. Following this, a sham MWM [18] will be applied and the movement previously selected will be repeated six to ten times in the first consultation. Briefly, the sham condition simulated the MWM procedure with a different hand positioning. The clinician, standing contralaterally to the treated shoulder, will place one hand over the superior aspect of the pectoralis major muscle and the other over the scapula, both hands will make skin contact only without any significant pressure. The participant will be informed that he or she should move to the onset of symptoms, if they occur.This process will be respected in every session, but from the second session onwards, two to three sets of 10 repetitions will be applied, with an interval of sixty seconds between sets. However, in case the sham MWM fails to improve the movement significantly, one set of six repetitions will be performed only**.**

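### The only harms question described asks participants to judge cause first, so the harms count reflects attribution rather than the randomised comparison

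*Protocol article*

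**What the plan says.** The Harms section of the protocol article gives the purpose of monitoring: "it is important to control for adverse events that might occur as a result of the procedures applied". The instrument follows: "In order to monitor these, this study will use an adapted questionnaire". Its quoted question is "Have you experienced any discomfort or unpleasent sensation as a result of this treatment". Participants then describe the sensation, rate it from 0 to 10, say when it began and say how far it disturbed their activities. On timing: "This scale will be applied at each treatment session".

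Four other parts of the article bear on how the question will be answered:

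- **Eligibility criteria, Table 1.** Inclusion requires "Scoring at least 3 out of 10 on a numeric pain rating scale", together with symptoms for more than 6 weeks and pain on active movement.
- **Exercise programme.** Loading is managed against a maximum pain score of 5/10. The control group's programme is "Exactly the same as the experimental group and conducted in the same way".
- **Sham MWM.** In the sham hold "both hands will make skin contact only without any significant pressure". The Background describes real MWM as including a passive glide force from the clinician.
- **Blinding.** "Blinding of participants will be analysed using a three point scale".

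No other section describes the collection of adverse events, and none describes a symptom question free of attribution.

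**The concern.** A randomised sham comparison can show whether MWM adds harm without anyone having to decide what caused a given symptom. If all symptoms are recorded in both arms, background symptoms balance in expectation, and the difference between arms estimates what MWM adds over sham. A question that admits only symptoms the participant blames on treatment gives up that advantage at the point of collection.

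The problem is sharper here because the most plausible harm, a pain flare, looks like the condition that brought the participant into the trial. A participant who puts a flare down to the old shoulder problem answers the question correctly with a no. An answer not recorded at the session cannot be recovered in the analysis. The Discussion says the trial should inform decisions on whether to include MWM, and the harms data are part of that.

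**Working it through.** The article gives no harms rate, so there is no figure of the plan to reproduce. Its one design calculation, the SPADI sample size, does not bear on this point except for the planned 35 participants per group.

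**Step 1: is there another route by which an unattributed event is counted?**

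- The 24-hour symptom check in the exercise programme concerns symptoms provoked by the exercise, so it too depends on attribution. It serves load adjustment.
- NPRS and SPADI (baseline, end of treatment, follow-up) and GROC (end of treatment, follow-up, scale down to −7) need no attribution. They are outcome scores at fixed times, are not stated as an event count, and can miss a short flare between sessions.
- Reasons for drop-out are to be reported, but they cover only those who leave.

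None of these replaces an event count free of attribution.

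**Step 2: what does the question record?** For one arm, let C be the number of symptom events caused by treatment (exercise plus MWM or sham) and U the number of unrelated events. Let a be the chance that a caused event is attributed to treatment, and b the chance that an unrelated one is. The expected recorded count is

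R = a × C + b × U.

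A question without attribution, fully answered, records C + U. Randomisation balances U in expectation, so its difference between arms estimates the difference in C.

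**Step 3: illustrations.** All values of C, U, a and b are assumptions. Events are per 35 participants: 40% of 35 = 14, and 20% of 35 = 7.

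| Case | EG recorded | CG recorded | Reading |
|---|---|---|---|
| C = 14 in both arms, U = 0, a = 0.5 in both | 0.5 × 14 = 7.0 | 0.5 × 14 = 7.0 | No spurious difference, but half the events are missed |
| C = 14 in EG and 7 in CG, U = 0, a = 0.5 in both | 0.5 × 14 = 7.0 | 0.5 × 7 = 3.5 | True difference of 7 events shrinks to 3.5 |
| C = 14 in both, U = 0, a = 0.8 in EG and 0.5 in CG | 0.8 × 14 = 11.2 (32%) | 0.5 × 14 = 7.0 (20%) | Spurious 12-point excess in EG |
| As above with the values of a exchanged | 7.0 (20%) | 11.2 (32%) | Same size, opposite sign |
| C = 7, U = 7, a = 0.8, b = 0.5 in both | 5.6 + 3.5 = 9.1 | 9.1 | More recorded than the 7 caused by treatment |

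The last row shows that under-counting is not guaranteed: the recorded count exceeds C whenever b × U is larger than (1 − a) × C, here 3.5 against 0.2 × 7 = 1.4.

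**Step 4: does the article fix the sign of any difference in attribution?** It does not. A participant who notices that the hold is light may be less ready to blame it. But sham participants are told to move to the onset of symptoms, while MWM repetitions normally run through pain-free range, so the sham may provoke symptoms more visibly. The shared exercise also gives both arms an obvious treatment-related cause for soreness.

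**The case against.** The case for leaving the question alone has substance.

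- The stated aim is to monitor events arising from the procedures, and the question matches that aim. No between-arm test of harms is described, and harms are not a primary or key secondary outcome. This stands and limits the point's importance, although any harms reported by arm still inherit the problem.
- The question is broad and is asked at each of ten sessions, so recall is short. This stands, but frequent asking does not remove the attribution.
- The instrument is an adaptation of a cited questionnaire whose full form is not shown. That a no answer skips the descriptive items is a natural reading, not something the article states. The point rests only on the wording of the question it quotes.
- Asking about any symptom in people with persistent pain brings in background fluctuation, and with about 35 per arm that noise could obscure a real difference. This is a genuine trade-off, which is why attribution should be kept as a second item.

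A reader might also infer that the question biases the comparison against MWM, because its recipients feel a real glide and sham recipients do not. The article does not support that. Treatment includes the exercise common to both arms, the direction of any attribution difference is open, and planning a check on blinding is not evidence that blinding fails.

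**Conclusion.** The point holds in a limited form. The only harms question the article describes makes the count depend on the participant's own view of cause, in people who already have the symptom most likely to be at issue. Flares may be missed and unrelated symptoms may be included. If attribution is equal in the two arms, no difference is created where none exists, though a real one can be diluted. If it differs by arm, harms reported by arm could be biased either way. That is a risk, not a demonstrated bias, and the shared exercise reduces it.

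A reader might infer that harms will necessarily be under-counted; wrong attribution of unrelated symptoms can push the count the other way. Size and direction cannot be derived from the document, and the counts worked through above show only the mechanism. The primary analysis is not touched, so this is a minor improvement, worth making because the lost information cannot be restored later.

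**What to change.** Since the questionnaire is already an adaptation, make four small changes:

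1. Replace the entry question with one that does not ask about cause, for example: since your last session, have you had any new or worse symptom or unpleasant sensation?
2. Keep the items on type, intensity, onset and interference with activities.
3. Add one separate item asking whether the participant thinks the symptom was related to the treatment.
4. Report all events by arm as the main harms summary, with attributed events as a supplementary count.

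The cost is one reworded question and one extra tick-box per session. Some unrelated background symptoms will be recorded in both arms, adding noise to the comparison, and the wording departs slightly from the cited questionnaire. The supplementary count preserves what the present question was meant to collect. Treatment, sample size and the primary analysis stay as they are.
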